**Figure 2 F2:**
[figure not shown]
Flow of participants. CRF, case report form.

### Study tests

The study will use a paired design, with all participants receiving the index tests and reference test during the same study assessment. The study will administer a total of six index tests (pre-bronchodilator peak flow and microspirometry and four screening questionnaires) and one reference test (post-bronchodilator quality diagnostic spirometry) to each participant.

#### Index tests

##### Lung function test - peak flow

A trained researcher will assess PEF using a simple peak flow meter (USPE, China). Each participant will perform three blows without administration of bronchodilator, after which the researcher will record the highest PEF. For the main analysis, PEF rates of <350 L/min for men and <250 L/min for women will be used to indicate a positive test.^18^

##### Lung function test - microspirometer

Microspirometry will be performed with minimal coaching by a trained researcher using a simple handheld microspirometer (Vitalograph COPD6), to measure forced expiratory volume (FEV)_1_, FEV_6_ and FEV_1_/FEV_6_ ratio. Each participant will perform three blows using the device, after which the researcher will record the highest FEV_1_ and FEV_6_ values, and the FEV_1_/FEV_6_ ratio. For the main analysis, FEV_1_/FEV_6_ ratios of <0.75^28^ and <0.78^29^ will be assessed to indicate a positive test.

##### Screening questionnaires

Four screening questionnaires will be used in the study; the COPD Diagnostic Questionnaire (CDQ),^17 30^ the COPD Screening Questionnaire (COPD-SQ),^19^ a symptom-based questionnaire^31^ and COPD Assessment in Primary Care To Identify Undiagnosed Respiratory Disease and Exacerbation Risk Questionnaire (CAPTURE)^18^(online supplemental appendix 1). The selection of questionnaires maximises symptoms being assessed and minimises duplication of items, while allowing comparison of the most relevant questionnaires. Recommended cut-points for each questionnaire will be used to identify those at risk of COPD for diagnostic spirometry, with potential additional analyses to explore optimal cut-points.

10.1136/bmjopen-2019-035738.supp1Supplementary data

#### Reference test

Post-bronchodilator quality diagnostic spirometry (20 to 60 min after administration of 400 μg salbutamol) will be performed by a trained researcher using a portable spirometer (Easy On-PC, NDD). Lung function data including FEV_1_, forced vital capacity (FVC) and FEV_1_/FVC ratio will be recorded in the NDD software, and will also be imported to the study REDCap database. Accuracy of the device flow heads will be verified at the start of each assessment day by the researchers; calibration is not required. Participants will perform a maximum of six blows, or less if repeatability within 100 mL or 5% is achieved (Association for Respiratory Technology and Physiology standards, 2013).^32^ For the purposes of this study, a COPD diagnosis will be defined as airflow obstruction based on the lower limit of normal using the Global Lung Initiative equations, according to post-bronchodilator quality diagnostic spirometry.

### Ordering of assessments

Index tests will be conducted before the reference test for all participants, and the reference test will be administered by a different researcher who will be blind to the previous test results. To decrease the potential training effect within the index tests, the order of the peak flow and microspirometer will be alternated, that is, approximately half of the participants will perform peak flow first and vice versa. The screening questionnaires will always be completed after administration of salbutamol, during the 20 to 60 min time frame permitted prior to the reference test. Due to use of pre-printed study material, the order of the screening questionnaires will not be alternated.

Besides that, participants’ standing height (stadiometer) and weight (scales) will be measured. Participants will also be asked to complete a study questionnaire by themselves, in a separate area of the assessment clinic, and return the completed forms to the researcher. The study questionnaire (online supplemental appendix 2) will include items relating to the following topics: demographic data (sex, age, marital status, education level and deprivation); smoking status; exposures (biomass smoke, occupational exposure to chemicals and particulates); health (medical diagnoses (including COPD, asthma, TB and so on), comorbidities and respiratory symptoms); quality of life (COPD assessment test). A member of the research team will be available to help participants to complete questionnaires if necessary.

10.1136/bmjopen-2019-035738.supp2Supplementary data

### Data collection

#### Study assessment

The study assessment will last approximately 80 min, including six stations. There will be two researchers at each assessment clinic to enable the assessments to run in parallel, and all data will be recorded on case report forms (CRFs), ensuring standardised data collection/recording.

At the end of the study assessment, researchers will provide all participants with information about the level of their airway obstruction, suggest they contact a doctor if appropriate and answer any immediate questions they may have. The flow of participants is presented in figure 2.

#### Resource use data

To calculate the healthcare costs of delivering each screening strategy, we will determine the unit costs and quantity of any equipment, medication and consumables required, as well as staff type and grade, staff time taken to deliver each individual test and use of facilities. The staff time taken will be collected with a simple questionnaire for researchers to fill in for each test (online supplemental appendix 3). Equipment costs (peak flow meters and spirometers) will be amortised over the estimated lifespan of the equipment. The cost per patient visit will be calculated using assumptions regarding the total number of patients the equipment will be used for. In addition, each individual test will be timed at a sample of assessment clinics so that an overall mean time and range for each test can be estimated.

10.1136/bmjopen-2019-035738.supp3Supplementary data

### Statistical methods

#### Sample size

The Alonzo method for paired test accuracy studies^33^ was used to calculate the sample size, assuming independence of tests and a prevalence of 12%, we will have 90% power to detect a difference in sensitivity of 10% (95% vs 85%^18 30 34 35^ with 1622 participants). If the sensitivity of tests is slightly lower in this population (90% vs 80%), we would have 90% power to detect this difference with a larger sample of 2279 participants.

#### Analysis plan

Data will be analysed using Stata V.15.

Our primary analysis will compare the performance of a screening questionnaire (CAPTURE) with a handheld device (peak flow meter). Secondary analyses will include the comparative performance of each index test, as well as a comparison of strategies where we use a screening questionnaire and a handheld device.

The performance of each index test when diagnosing COPD (confirmed by quality diagnostic spirometry) will be investigated by presenting 2×2 tables and calculating the sensitivity, specificity, positive predictive value and negative predictive value, along with 95% CIs. For the tests with a continuous score, receiver operator curve analysis with area under the curve (with 95% CIs) will be produced. Comparisons of test accuracy between different index tests and different test strategies will be conducted using McNemar’s test and logistic regression modelling.

Sensitivity analyses will explore the impact on test performance of the index tests and strategies when using different definitions of COPD, including (i) a combination of spirometry data and clinical confirmation, and (ii) using the GOLD definition (fixed ratio (FEV_1_/FVC <0.7)) of airflow obstruction. Additional sensitivity analyses may explore the impact of spirometry quality as well as exploring optimal cut-points for the screening tests, in recognition that test performance will be dependent on the cut-points used.

A fully incremental cost-effectiveness analysis will be undertaken from a healthcare perspective to calculate the cost per true case detected for all pre-determined strategies. The strategies (including combinations) will be ordered by the number of true cases detected, from least to greatest, and the principles of dominance and extended dominance will be applied to eliminate redundant strategies from the analysis. Sensitivity analysis will be undertaken to explore the impact on results of any changes in assumptions, for example, time taken for a strategy.

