While COPD screening programmes are not currently recommended by the USA^14^ or UK^15^ due to insufficient evidence of health benefits, the national policy do recommend screening for undiagnosed COPD in China.^11^ Despite the support for screening in China, there is no recommendation on the best strategy or approach to use. Multiple screening questionnaires have been developed to identify patients at risk of COPD, either in primary or secondary care settings.^16–20^ Questionnaire items include the presence of respiratory symptoms (eg, wheeze, dyspnoea and cough) while some tools also explore exposures, smoking history and age. The questionnaires are all designed to be self-completed, but vary regarding the populations in which they were developed/validated, for example, general population or targeted groups such as symptomatic patients or current smokers. Microspirometers are small handheld devices that measure lung function, which are low cost, quick to use and require minimal coaching for patients. Peak flow monitors are simple, low-cost devices that measure how much air patients can expel during a forced expiration (peak expiratory flow, (PEF)), and evidence indicates that these devices may also be suitable as a possible screening tool for COPD.^18 21 22^

Screening tests can be used individually or in combination as screening ‘strategies’. Systematic reviews and more recent primary studies typically assess the use of a single test, concluding that many of the available tests may be appropriate for use in COPD screening.^23–25^ However, studies in community settings in China are limited and it is not known which screening test or strategy would be most appropriate to use. As a middle-income country with a large potential COPD population, it is important to explore the most effective and cost-effective screening strategy. Accurately detecting individuals who merit referral for quality diagnostic spirometry could minimise the number of ineligible referrals, thus protecting health system resources and ensuring appropriate and timely treatment for those subsequently diagnosed.

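### The stated cost-effectiveness method removes strategies by dominance with no allowance for sampling error, and does not say whether spirometry is charged to every screen-positive

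*Protocol article*

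**What the plan says.** The Analysis plan of the protocol article sets out the economic method in three sentences. The first gives its type: "A fully incremental cost-effectiveness analysis will be undertaken from a healthcare perspective to calculate the cost per true case detected for all pre-determined strategies". These strategies, combinations included, "will be ordered by the number of true cases detected, from least to greatest", and then "the principles of dominance and extended dominance will be applied to eliminate redundant strategies from the analysis". On uncertainty it adds: "Sensitivity analysis will be undertaken to explore the impact on results of any changes in assumptions, for example, time taken for a strategy". For accuracy, the same section plans "calculating the sensitivity, specificity, positive predictive value and negative predictive value, along with 95% CIs", and comparisons of tests and strategies by McNemar's test and logistic regression.

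On costs, Resource use data covers the delivery of each screening strategy: "we will determine the unit costs and quantity of any equipment, medication and consumables required", together with "staff time taken to deliver each individual test and use of facilities". It also amortises peak flow meters and spirometers.

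The Aim is to find the most effective and cost-effective strategy, and the Discussion says the study will establish which one is best. The Introduction gives a reason for accurate screening: it "could minimise the number of ineligible referrals, thus protecting health system resources".

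**The concern.** The number of true cases a strategy detects is an estimate from a sample, not an assumption. The stated sensitivity analysis varies assumptions, so it does not address how far that count could move in another sample. Dominance is an all-or-nothing rule: a strategy judged redundant leaves the analysis. If two strategies are close, a few cases can decide which one goes, and the resulting frontier carries no measure of how secure it is. Combinations that share a component test may well lie close together.

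The second part concerns specificity. The effect measure counts true cases only, so a false positive can count against a strategy only through cost. Under Screening questionnaires, a positive result leads to diagnostic spirometry. Whether that spirometry is charged to each strategy for all its screen-positives therefore determines whether specificity affects the economic result at all. Neither Resource use data nor the Analysis plan states it.

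**Working it through.** **Inputs from the article.** Planned recruitment is about 2000 (Abstract). Prevalence is 12% and the tests are taken as independent (Sample size). Expected cases: 0.12 × 2000 = 240.

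**Reproducing the article's own figures.** The Alonzo paired formula, with two-sided α = 0.05 (assumed, as none is stated), 90% power, g = ratio of sensitivities S₁/S₂, and joint positivity S₁S₂ under independence:

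cases = (3.2415 / ln g)² × [(g + 1)S₂ − 2S₁S₂] / (g S₂²)

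- 95% v 85%: 194.6 cases; 194.6/0.12 = 1622.
- 90% v 80%: 273.5 cases; 273.5/0.12 = 2279.

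Both match the Sample size section. They concern one pair of tests 10 points apart. The article gives no precision figure for the economic analysis.

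**Chance that the order by cases is wrong.** For true sensitivities a > b in 240 cases with independent tests:

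SE of the difference = √{[a(1−b) + b(1−a) − (a−b)²] / 240}

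Example, 85% v 80%: √{[0.170 + 0.120 − 0.0025]/240} = 0.0346. The normal approximation gives Φ(−0.05/0.0346) = 7.4%. Counting exactly the samples in which the weaker test detects strictly more cases gives 6.6%.

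| True sensitivities | SE (points, independent) | Wrong order, independent | Correlation 0.3 | Correlation 0.5 |
|---|---|---|---|---|
| 95% v 85% | 2.7 | <0.01% | <0.01% | <0.01% |
| 90% v 80% | 3.2 | 0.07% | <0.01% | <0.01% |
| 85% v 80% | 3.5 | 6.6% | 3.6% | 1.6% |
| 90% v 85% | 3.0 | 4.1% | 1.9% | 0.7% |
| 90% v 88% | 2.9 | 22% | 18% | 14% |

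The 5-point and 2-point pairs and the within-case correlations are assumptions; the 10-point pairs are the article's.

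What a wrong order does depends on cost. If the truly more sensitive strategy is also the dearer one, a reversal makes it look dominated and it is removed. If it is the cheaper one, a reversal keeps a strategy that is truly dominated.

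**Whether spirometry is charged to screen-positives.** Assumed units: index test 10, spirometry 50, prevalence 12%. Strategy L has sensitivity 95% and specificity 50%; strategy H has 85% and 85%.

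- True cases per person screened: L 0.12 × 0.95 = 0.114; H 0.12 × 0.85 = 0.102.
- Screen-positives per person: L 0.114 + 0.88 × 0.50 = 0.554; H 0.102 + 0.88 × 0.15 = 0.234.
- Spirometry not charged: both cost 10. L finds more cases at the same cost, so H is dominated and removed.
- Spirometry charged: L costs 10 + 50 × 0.554 = 37.7; H costs 10 + 50 × 0.234 = 21.7. H is cheaper and stays. L's incremental cost is (37.7 − 21.7)/(0.114 − 0.102) = 1,333 per extra case.

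A second assumed pair shows the switch point. A has sensitivity 90%, specificity 50%, test cost 1; B has 88%, 80%, test cost 2. With spirometry cost c, A costs 1 + 0.548c and B costs 2 + 0.2816c. A dominates B until c = 1/0.2664, about 3.75 units; above that, B is not dominated.

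**The case against.** The strongest objection is that this is an article. Ordering by effect and applying dominance is standard incremental analysis and is compatible with a bootstrap or a probabilistic analysis, which a fuller economic plan may contain. A reader might infer that the article commits to point estimates alone. It does not use those words, and it does not rule out resampling. That part of the objection stands. It does not dispose of the point, because the article does set out the economic method (perspective, outcome, ordering, elimination and sensitivity analysis), and the uncertainty step it chose to state does not cover sampling error. The confidence intervals and McNemar comparisons concern accuracy and do not enter the frontier.

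A second objection is that the risk is small for the differences the study was sized to find. That is correct: a 10-point gap reverses in fewer than 0.1% of samples, and positive correlation shrinks the risk for closer pairs. A changed order also removes a strategy only when the costs point the same way.

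On costs, a reader might infer that diagnostic spirometry is left out. The documents do not support that. Resource use data names spirometers and medication, and the only medication described in the assessment is the salbutamol given before the reference spirometry (Study tests; Reference test). The list can therefore be read to include it, though spirometers could also mean the microspirometer alone. What remains is that nothing says it is charged to each strategy's screen-positives.

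**Conclusion.** The point holds in a limited form. As stated, the economic analysis produces a frontier with no measure of sampling uncertainty, while the Discussion promises a firm choice of strategy. The exposure is confined to close strategies: about 4–7% wrong order at a 5-point difference and about 22% at 2 points, with 240 cases and independent tests; 0.7–3.6% and 14–18% respectively at correlations of 0.3 to 0.5. It is negligible at 10 points.

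The cost point is a gap in specification. Under assumed unit costs and specificities, charging spirometry to all screen-positives decides whether the more specific strategy is eliminated. Two stronger readings do not follow. Charging spirometry does not reverse the ranking: the order by true cases is unchanged, and in the first example both strategies then stay on the frontier. Nor do low-specificity strategies win as a matter of course, since dominance also depends on test cost. The article does not list the strategies, their number or the rules for combining tests, so no figure for over-optimism in the selected strategy can be derived from it.

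**What to change.** Add to the economic analysis a non-parametric bootstrap of participants, stratified by centre, keeping all tests of a person together. In each sample, recompute cases and costs and rebuild the frontier. Report each strategy's probability of being on the frontier and intervals for incremental cost per true case. Keep the planned sensitivity analysis for unit costs and test times, which participant resampling does not cover.

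State in Resource use data or the Analysis plan that each strategy's cost includes post-bronchodilator diagnostic spirometry for all its screen-positives, true and false.

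All participants receive every index test and the reference test, so no new participant data are needed; the work is a few hours of programming. The downside is that the conclusion may be less clear-cut, and the Discussion's wording about settling the best strategy may need softening to match.

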### Training

A 2-day training event will be organised for all researchers to ensure standardised study processes are followed at all research sites. Training will cover study processes and assessment techniques as well as expert teaching regarding respiratory physiology and spirometry lung function tests. Researchers’ competency in conducting spirometry will be certified at the end of the training. Spirometry traces from practice sessions will be over-read by an expert to ensure sufficient quality prior to participant recruitment commences. Local respiratory specialists will over-read all spirometry tests during the study period, to ensure quality is maintained. During site initiation visits, the study team will observe a complete study assessment to ensure researchers adhere to the study protocol. The study will conduct monitoring site visits throughout the study period.

### Patient and public involvement

The research team conducted a research prioritisation exercise with patients, clinicians and policy makers, and the need to identify effective screening strategies for undiagnosed COPD was one of the research areas prioritised. All stakeholders involved in this exercise will receive study updates twice a year, will be kept informed of findings and will be consulted at the end of the study regarding implications for practice and policy decisions, as well as advice on appropriate dissemination of study findings.

A patient advisory group (PAG) has been set up, which is funded to meet at approximately quarterly intervals or according to need, and will advise on a range of aspects of the design, conduct, analysis and dissemination of the study. The PAG will discuss issues as requested by the CIs and the chair will report their comments back to the investigators.

In addition, the study has a trial steering committee (TSC) that meets regularly and comprises various independent members, including a patient and a clinician representative as well as international experts in respiratory research. The TSC also includes several members of the study research team.

## Ethics and dissemination

### Ethics and informed consent

The study has been approved by the Peking University First Hospital (2018-R-141, PUFH) (online supplemental appendix 4) and the University of Birmingham (ERN_18–1177, UoB) (online supplemental appendix 5). Residents responding to the study invitation will be given the study information sheet with enough time to read it and will have opportunity to ask the researcher any questions about the study. Interested respondents who are eligible for the study will be asked to sign a consent form (online supplemental appendix 6), or if unable to consent, a family member will be asked to sign on their behalf. Consent will also be sought to allow the research team to contact participants about future studies related to the Breath Well programme; this is optional and will not affect eligibility for the study described in this paper.

10.1136/bmjopen-2019-035738.supp4Supplementary data

10.1136/bmjopen-2019-035738.supp5Supplementary data

10.1136/bmjopen-2019-035738.supp6Supplementary data

### Indemnity

The study is not an intervention study, and as such poses low risk to participants. However, clinical insurance was purchased in case of serious adverse events.

### Data storage

Study data will be entered into a bespoke REDCap online database. All electronic data held by the research team will be password-protected and stored on encrypted study laptops. Paper-based data will be held in locked filing cabinets in the study office in each site. The research team will conduct monitoring visits of all research sites during the recruitment period to ensure data are being collected, entered and stored according to pre-specified study working instructions.

### Dissemination and publication policy

Study results will be published in peer-reviewed journals and presented at national and international conferences, as well as relevant community/stakeholder engagement activities. Participants who explicitly express a wish to be informed about the research outcome will be contacted and offered to receive an article or poster with a lay summary of the study.

